### Ethical considerations

Written informed consent will be obtained from every participant and fingerprint impressions will be taken from consenting illiterate participants. Patients identified as having depression or endorsing the suicide item on PHQ-9 will be referred to appropriate professionals for further assessment and management. Permission to conduct the study has been sought from the the district health officers of Lilongwe, Kasungu, Dedza, Mchinji, Salima and the hospital director of Kamuzu Central Hospital. Study participants will not be given any financial reimbursement, however they will thanked verbally for their participation. Privacy will be maintained as the interviews will be conducted in a room which will provide both visual and audio privacy. Referrals will be made to appropriate professionals for further assessment and management of cases where participants will be identified to be under depression as well as cases that will screen positive for suicidal ideations through the interviews.

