## Aims and objectives

Our overall objective is to evaluate the effectiveness of integrating screening and depression management into physical NCD routine care on patient and service outcomes in Malawi. In this way, we will contribute to evidence on comorbidity of depression and diabetes including the effects of identifying and treating depression in patients with comorbid diabetes and depression in physical NCD care in Malawi.

Our study has four specific objectives:To determine the sensitivity and specificity of the Patient Health Questionnaire-9 (PHQ-9) in the detection of depression in NCD clinics.To estimate the prevalence of comorbidity between depression and diabetes mellitus in Malawi.To determine detection rate of depression in physical NCD clinics in Malawi.To compare patient outcomes in physical NCD clinics with and without integration of depression screening and management.

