## Research questions

The main research questions in this study are:Will the validated Chichewa PHQ-9 demonstrate satisfactory sensitivity and specificity in physical NCD clinic settings in Malawi?Will integrating depression screening using a validated PHQ-9 and depression management (based on a specially designed toolkit) be more effective than usual care in identifying patients with comorbid depression and diabetes, facilitating treatment of depression in patients with comorbid depression and diabetes, and improving clinical outcomes among patients with comorbid depression and diabetes?

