#### Usual care

This would involve the NCD clinicians treating patients with comorbid depression and diabetes using normal practices of treating depression involving antidepressants.

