## Recruitment and data collection

We will use a mixed-methods (quantitative and qualitative) approach in phase II. The reason for collecting both quantitative and qualitative data is to complement and also to address the shortfalls of either approach. The use of both forms of data allows researchers to gain deeper understanding of the phenomenon under study.^31^ In addition, evidence suggests that triangulation of methods increases both the validity and reliability of data.^32^

The research assistant with the help of health professionals running the NCD clinic at each site will identify the study participants who meet the inclusion criteria consecutively. The research assistants will provide information about the study to the patient and seek written informed consent. Participants will be eligible for the study if they are at least 18 years of age, are attending the NCD clinic for diabetes care and are available for an interview. Participants will be excluded if they require acute medical care or are unable to speak. The research assistants will enrol patients who consent and carry out interviews at the health facility. When patients do not consent to participate in the study, the research assistant will request permission to record sex, age, level of education and occupation of the patient. Adult patients with poorly controlled diabetes (a HbA_1_c level of 8.5% or higher as suggested from previous research^30 33^) and comorbid depression will be recruited for the study and followed up to 6 months after recruitment (figure 3). Data collection will occur at three time points: baseline, at 3 months and at 6 months.

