## Measurements

### The primary exposure variable

Depression will be measured using PHQ-9. PHQ-9 will have been validated in phase I of this study.

The primary exposure of interest is whether the patient is receiving care at an intervention or usual care facility.

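### Phase II enrols only patients already identified as depressed, in both arms, so it cannot compare identification with usual care, and its comparator is not described consistently

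*Protocol article*

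**What the plan says.** All references are to the protocol article.

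- **Question.** Under Research questions, integration is to be tested for whether it will "be more effective than usual care in identifying patients with comorbid depression and diabetes, facilitating treatment of depression", and for whether it improves clinical outcomes.
- **Entry.** Under Phase II, Recruitment and data collection, adults with HbA1c of 8.5% or higher and "comorbid depression will be recruited for the study and followed up to 6 months after recruitment". On who finds the patients eligible under these criteria: "The research assistant with the help of health professionals running the NCD clinic at each site will identify the study participants who meet the inclusion". This applies to all four clinics.
- **Measurement.** Under The primary exposure variable: "Depression will be measured using PHQ-9". The Primary outcome variable section schedules the PHQ-9 at baseline, 3 months and 6 months, with no limit to one arm.
- **Outcomes.** HbA1c and depression are co-primary, and quality of life (EQ-5D) is secondary.
- **Control arm.** Usual care is "NCD clinicians treating patients with comorbid depression and diabetes using normal practices of treating depression involving antidepressants".
- **Intervention arm.** The Intervention section trains clinic staff to screen, draw up and follow care plans, prescribe and monitor antidepressants, and use problem-solving techniques.
- **Referral.** Under Ethical considerations: "Patients identified as having depression or endorsing the suicide item on PHQ-9 will be referred to appropriate professionals for further assessment and management". The same section makes the point a second time for participants found depressed through the interviews. It lists permissions from the four Phase II districts as well as Lilongwe.

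**The concern.** A trial can compare how well two systems identify patients only if patients enter before identification has happened. Here identification is a condition of entry in both arms, so one limb of the main question has no contrast behind it.

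The second issue is what the control arm represents. The Introduction argues that depression is probably poorly detected in these clinics, which is the rationale for integration. The enrolled controls, however, have been found by the study, with help from their own clinic's staff, and the referral statement reads as applying to them too. The sections on intervention, usual care and ethics do not give one consistent account of what either arm receives once depression is known.

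At stake is the conclusion. The Dissemination plan promises policy briefs on integration. A positive result could be reported as showing better identification, which this cohort cannot show. A null result could be reported as integration adding nothing to usual care, when the comparator was care after study identification, possibly with referral. The Limitations section does not mention this.

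**Working it through.** **Step 1. Identification by arm.** Let p be the proportion of enrolled patients whose depression has been identified at entry. The entry criterion applies at every site, so p = 1 in the intervention arm, p = 1 in the control arm, and the difference is 1 − 1 = 0. This does not depend on how the referral statement is read.

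**Step 2. Is the limb measured elsewhere in Phase II?** The listed outcomes are HbA1c, PHQ-9 and EQ-5D. None is a between-arm measure of detection by clinic staff or of starting depression treatment. A log of patients screened for entry would not fill the gap, because the research assistant takes part in the finding and the log would not isolate what the clinic detects by itself.

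**Step 3. What each arm receives.**

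| Section | Intervention clinics | Control clinics |
|---|---|---|
| Recruitment and data collection (Phase II) | identified at entry | identified at entry |
| Primary outcome variable | PHQ-9 at baseline | PHQ-9 at baseline |
| Intervention / Usual care | managed by trained clinic staff | clinicians' normal practice; no study screening or referral mentioned |
| Ethical considerations | referred if depressed | referred if depressed |

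The undefined term is who counts as an appropriate professional.
- If it means people outside the clinic, controls gain a referral that the Usual care section does not mention, and intervention patients are referred away from the staff trained to manage them.
- If it means the clinic's own staff, control clinicians are told which patients are depressed.

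Either way, controls have been identified by the study.

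**Step 4. Reproduce the plan's sample size.** Inputs from Sample size determination (Phase II): difference 0.7%, SD 1.8%, correlation 0.5, 5% significance (two-sided assumed), 80% power, 10% dropout.

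- Residual SD = 1.8 × √(1 − 0.5²) = 1.559
- n per group = 2 × (1.960 + 0.842)² × 1.559² / 0.7² = 77.9, rounded up to 78
- 78 / 0.90 = 86.7, rounded up to 87 per group; total 174

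All three figures match the plan.

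**Step 5. Illustration of dilution.** The documents give no dilution figure. Assume that 0.7% is the contrast against undisturbed usual care, and that identification and referral of controls remove a share f of it.

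- SE = 1.559 × √(2/78) = 0.2496
- Power = Φ(0.7(1 − f)/0.2496 − 1.96)

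| Assumed f | Contrast | Power at 78 per group | Evaluable n per group for 80% |
|---|---|---|---|
| 0% | 0.70% | 80% | 78 |
| 10% | 0.63% | 71% | 97 |
| 20% | 0.56% | 61% | 122 |
| 30% | 0.49% | 50% | 159 |
| 40% | 0.42% | 39% | 217 |
| 50% | 0.35% | 29% | 312 |

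Like the plan's own calculation, this works at the level of individuals and makes no allowance for clustering by clinic.

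**The case against.** The strongest reply is that the sections can be read together. The ethics paragraph is general and covers both phases, and the appropriate professionals may be the clinic's own clinicians: trained staff in the intervention arm, staff following normal practice in the control arm. Usual care is itself defined as treating patients who have depression, so recognised depression is part of the stated comparator. Objective 4 concerns patient outcomes, and HbA1c and PHQ-9 can be compared between arms in an identified cohort.

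Much of this stands. The referral text is ambiguous; it is not a proven contradiction, and the outcome comparison remains valid against whatever comparator is delivered. The reply does not rescue the identification limb, which fails on the entry criterion alone. Nor does it restore an untouched usual-care arm, since telling control clinicians who is depressed is itself part of what integration is meant to supply.

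A reader might infer more than the documents support:

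- **That the detection-rate objective ("To determine detection rate of depression in physical NCD clinics in Malawi") has no data.** It is not tied to Phase II or to a comparison of arms. In Phase I the clinic consultation falls between the PHQ-9 and a masked SCID, so a detection rate may come from there.
- **That the treatment question cannot be answered at all.** Referral is not treatment received, and treatment could still differ by arm. The comparison is blurred, and no outcome is listed for it.
- **That power is known to fall to a particular figure.** The 0.7% is presented as a clinically important difference, informed by an earlier study whose comparator the article does not describe. Nothing shows that dilution occurs or how large it is.

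**Conclusion.** The concern holds in two parts of different strength.

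The first is certain. Among Phase II participants the difference in identification is zero by design, and no listed outcome measures detection or treatment initiation by arm. The identifying limb of the research question cannot be answered from this cohort.

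The second is a matter of inconsistent description. The article does not settle whether controls receive only normal practice or normal practice plus referral. On either reading they have been identified by the study, so the comparator may be enhanced relative to the poorly detecting usual care that motivates the trial. The effect on the HbA1c contrast is unknown. The fall in power to between about 71% and 29% rests wholly on the assumed 10% to 50% dilution.

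The stated sample size is arithmetically correct, and the primary ANCOVA can be carried out as planned. What has to change is the claim that the comparison can carry. The referral safeguard is not in itself an error.

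**What to change.** 1. Reconcile the sections Research questions, Intervention, Usual care, Recruitment and data collection (Phase II) and Ethical considerations, including who the appropriate professionals are in each arm. The pathway is for the investigators and the ethics committee to decide.
2. Describe the control arm as it will be delivered, stating the study's own PHQ-9 identification and any referral that follows.
3. Limit the Phase II question and conclusion to the outcomes of integrated management against that comparator among patients already identified as depressed. Remove the between-arm identification claim.
4. For enrolled participants, record referral and depression treatment received at the planned 3- and 6-month visits, and tabulate both by arm.

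The cost is rewording and a few extra data fields at visits already scheduled. The downside is a narrower claim. It would be tempting to keep the identification limb by extracting clinician-noted depression from the mastercard for all attenders. The article mentions that record only for the diabetes outcome, and nothing says that it holds depression data or could be used for patients not enrolled, so the fix does not rely on it.

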### Dissemination plan

The findings will be disseminated through publications in peer-reviewed journals and conference presentations. Summary reports will be submitted to the participating institutions and to the University of Malawi, College of Medicine. The results will also be shared with policy makers and other local stakeholders in the form of policy briefs as part of evidence on integration of depression management in NCDs.

### Limitations of the study

In this study, people may have undiagnosed comorbid illnesses and our method of screening may not be strong in capturing other comorbid illnesses. In the first phase of validation we will use two specialised clinics which may not be representative of the wider population. QoL will be measured using five domains and we will therefore not obtain detailed information on the various dimensions that assess health-related QoL. The quasi-experimental design which will be used in the second phase also has a limitation that baseline differences between the clinics may lead to spurious results.

### Strengths of the study

This study will provide the much needed evidence about the impact of comorbid depression on the outcome of diabetes. The cross-sectional study design will allow us to estimate the prevalence of depression among people with diabetes. The study will enable us to investigate the impact of depression in determining the outcome of diabetes. To our knowledge, this study will be the first in Malawi to examine identification and interventions for depression in physical NCD clinics.

### Expected benefits of the findings

Our findings will contribute to sparse evidence on mental health, diabetes and other NCDs in LMICs. We anticipate that our study findings will raise awareness of comorbidity among clinicians, service providers, policy makers and that it will contribute to clinical practice and policy change regarding the delivery of mental healthcare in NCD care in Malawi.
